### Reaction time, attention & working speed

Physical efforts when performing standardized tests (e.g. standing or walking) can negatively influence cognitive parameters [28, 29]. As studies reporting deterioration of work-related outcomes were all of short duration [19] and there are indications that these are caused by non-familiar working conditions, long-term effects on cognitive performance remain to be identified. Within the study protocol, three different performance-related tests were implemented:

A digital text editing task encouraging participants to fill in spaces in an ergonomic guideline text for 10 min was used. A Stroop-Color-Word-Conflict (Stroop) test, used to measure selective attention and processing speed [33–35] as well as a “d2R-test of attention” (d2R), commonly used in the European area to determine concentration performance [36–38], were implemented.

The simplicity of the text editing task (that did not require any disciplinary knowledge) enabled working speed measurements and simulated typical low effort office work. The implemented digital Stroop-test version contained 190 congruent, incongruent and neutral tasks and required approximately 10 min to simulate long-lasting monotonous office screen work. The d2R-test was executed as a pen and paper version. Therefore, it enabled screen breaks during the test protocol and simulated paper-related office work.

The Stroop-test and the d2R-test are both characterized by a high test-retest reliability (*r* = 0.77–0.95) and do not require any specific previous knowledge except of rudimentary language skills [39, 40]. Normative values for the d2R-test are available for different countries [39].

### Workload perception

Sit-to-stand workstations can evoke positive as well as negative associations [22]. While additional physical efforts caused by standing can lead to higher discomfort especially in the lower extremities (e.g. leg swelling) [22], novel working environments can improve mental well-being [41]. A common method to rate workload perception is the NASA-TLX questionnaire [42]. For reasons of simplicity and unmodified sensitivity [42], the short version of this questionnaire (RTLX), consisting of six major items, was used. Influences on workload perception based on unweighted items in the RTLX were negated due to the cross-over design.

### Salivary cortisol level

Although there are new findings related to the metabolic risks associated with postural changes (breaks in sedentary time) [16, 43, 44], the effect on stress-related parameters is still unclear. Modified cortisol levels after implementing a novel workplace have been shown but the effect of postural changes on cortisol level is not yet known [41]. Therefore, salivary cortisol level was measured during the study protocol and on the following morning in order to detect the cortisol awakening response (CAR) [45].

### Heartrate variability

Heartrate variability (HRV) can be used for predicting all-cause mortality and characterizing cardiovascular health [46, 47]. Improvements of HRV caused by additional physical effort have been shown mainly in physical training programs with medium or vigorous intensity [48–50]. Additional weekly metabolic efforts around 1000 METmin at low intensity level (walking) have also demonstrated positive changes in HRV [51]. Since additional standing (caused by occupational sitting time reduction) should lead to the same level of physical effort (assumption 20–30 % standing), any effect on HRV would be detectable. The 30 min breaks within the study protocol as well as nocturnal periods were used to compare HRV under bias reduced conditions. According to the HRV guideline [46], 24 h Holter monitoring measurements have been implemented. HRV will be analyzed using the software Kubios [52].

### Controlling for outside of work physical activity and sedentary behavior

Physical activity and sedentary behavior are related to physiological and cognitive changes [53, 54]. To avoid bias these parameters have to be determined. The International Physical Activity Questionnaire (IPAQ) has been shown to be reliable and valid for estimating physical activity and sitting time without any further measuring device [55–57]. The long version of this questionnaire (IPAQ-long) additionally enables it to distinguish between occupational and non-occupational activity. To adjust for outside of work sedentary behavior and/or physical activities, the IPAQ-long was interview administered at the beginning of each laboratory measurement day.

### Body movements

Body movements can alter physiological parameters and cognitive performance [28, 58]. Especially small movements during longer time intervals are very hard to classify my means of personal observations. Therefore, a three-dimensional accelerometer – placed on the sternum via a neoprene breast belt – was used to objectively measure body movements. Upper body placements of accelerometers have been shown to reliably detect body movements, and sit-to-stand as well as stand-to-sit transitions [59, 60]. To reduce the total number of sensors, a HRV-recorder with integrated 3D-accelerometer was used (model: medilog AR12 plus, Schiller AG, Baar, Switzerland).

### Measurement protocols

To test the study hypotheses, several parameters were defined and/or measured under standardized (laboratory measurements) and real life (field measurements) conditions (Table 1). Whereas body postures as well as postural changes were collected continuously during the 23-week intervention period, all further parameters were selectively measured before and after the intervention. To guarantee similar test sequences for each participant, a study protocol for laboratory measurements was developed (Fig. 3), consisting of three phases collecting physiological and cognitive parameters.

**Table 1 Tab1:** Parameters measured within the ACTIVE OFFICE study

Measurement			Location		Data points	Sampling rate
Parameter	Method	Performed by	Laboratory	Office	d^-1^ (overall)	s^-1^
*Physiological*						
Sitting time	IPAQ-long	questionnaire - interview	x		1 (4)	n.a.^d^
Physical activity	IPAQ-long	questionnaire - interview	x		1 (4)	n.a.^d^
Mental workload	NASA-TLX	questionnaire	x		1 (4)	n.a.^d^
Salivary cortisol	saliva collection	Salivette + cortisol ELISA	x^a^		8 (32)	n.a.^d^
Heart-rate	ECG	ECG recorder	x^b^		n.a.^c^	250
Body movements	acceleration	ECG recorder	x^b^		n.a.^c^	250
*Cognitive*						
Working speed	text editing task	computer software (matlab)	x		5 (20)	>1000
Reaction time	Stroop-test	computer software (matlab)	x		5 (20)	>1000
Attention	d2R-test	test sheet	x		5 (20)	n.a.^d^
*Office based*						
Body postures	logging tool	computer software (C#)		x	n.a.^c^	>1000
Postural changes	logging tool	computer software (C#)		x	n.a.^c^	>1000

^a^Seven measurements in the laboratory followed by one measurement at home on the following morning

^b^Measurement starts in the laboratory and ends at home on the following morning

^c^Data points depending on duration of measurement

^d^Non-digital measuring method (pen & paper)

**Fig. 3 Fig3:**
[figure not shown]
ACTIVE OFFICE study protocol (laboratory measurement)

In the first (initial) phase, participants were familiarized with the study protocol. Sitting time and weekly physical activity were determined via the IPAQ-questionnaire. Examples of each cognitive test implemented in the cognitive phase were executed according to their guidelines [39]. A 30 min break in a sitting posture was used to ascertain baseline heart-rate and cortisol level. Baseline heart-rate was calculated after a 20 min rest for a 5 min interval and saliva samples were collected at the end (30 min) of the break.

In the second (cognitive) phase subjects participated in a test battery containing five blocks. Each block consisted of a working speed test (text editing task), an attentional test (d2R-test of attention) and a reaction time test (Stroop-test). These tests lasted for 30 min to fulfill recommendations regarding postural changes [24]. To simulate “common” working conditions (computer based and non-computer based tasks), digital (text editing task, Stroop-test) as well as pen & paper (d2R-test) versions of the implemented tests were used. All blocks were executed in alternating postures (sit – stand – sit – stand – sit) and at the end of each block – after a 5 min break – salivary samples were collected. The order of posture was not changed within groups or time.

In the third (final) phase participants were asked to estimate their workload by means of the NASA-TLX questionnaire followed by a 30 min resting phase in a sitting posture. During both 30 min resting phases (initial & final) participants watched documentaries and were encouraged not to talk.

Salivary samples were collected after each break during the study protocol and on the following morning, 20 min after waking up, to ascertain cortisol awakening response (CAR). Salivary samples were centrifuged and stored at -80 °C for subsequent testing using a chemiluminescent immunoassay.

Heart-rate was measured from the start of the study protocol until the CAR measurement.

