## Outcome measures

Measurements were made both in the field and in a laboratory. Field measurements were made and processed continuously over the 23-week intervention period. Laboratory measurements were made on two different days, 1 day prior to intervention, and 1 day following intervention (due to cross-over design, each subject underwent 4 total days of laboratory measurements). Field measurements were collected automatically at the participants’ workstation in their working office. Laboratory tests were conducted in a controlled, simulated work-space located at the University of Applied Sciences Campus Linz.

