### Outcomes

Primary outcomes were changes in sitting time after 23 weeks in the experimental group compared with its own control period and the control group.

Secondary outcomes within the experimental group were changes in: reaction time, working speed, level of attention, workload perception, physical activity and postural changing pattern for the intervention phase as compared to the control phase.

Tertiary outcomes were changes in salivary cortisol level and heartrate variability (HRV) within the experimental group.

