### Experimental group: laboratory measurements

All laboratory measurements were made in a controlled laboratory at the campus site Linz of the University of Applied Sciences Upper Austria. Temperature, air flow, humidity, lighting conditions (artificial light only) and noise level were controlled and set to be consistent with the subjects’ typical working environment.

Participants were asked to refrain from exercise, caffeine and alcohol and undue stress for 24 h prior to laboratory testing. Food intake 90 min prior to the experiment was prohibited. Subjects were instructed to pursue their usual professional activity in the morning, followed by a laboratory visit in the early evening. To avoid daily fluctuations on performance all measurements started between 1:30 and 2:45 pm.

During the laboratory measurements, subjects either stood or sat upright in an ergonomic office chair, according to the study protocol. Subjects were encouraged to work as fast and as accurately as they could. To ensure identical testing conditions between subjects and to not unduly influence physiological parameters such as salivary cortisol level or heart rate variability, subjects were required to minimize excessive movement (e.g. standing up during the sitting periods). During regular breaks subjects were allowed to visit the toilet. Minor body movements, which typically occur under normal working conditions, were allowed.

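### The single saliva sample taken 20 min after waking gives a cortisol level, not the cortisol awakening response it is said to capture; the 24 h Holter description also needs reconciling with the recording window

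*Protocol article*

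**What the plan says.** **Cortisol.** The Salivary cortisol level section gives the purpose: "salivary cortisol level was measured during the study protocol and on the following morning in order to detect the cortisol awakening response (CAR"). The text after Fig. 3 in Measurement protocols fixes the morning time point: "on the following morning, 20 min after waking up, to ascertain cortisol awakening response (CAR"). Table 1 lists 8 saliva data points per day and 32 overall, with the footnote "Seven measurements in the laboratory followed by one measurement at home on the following morning". Outcome measures states that "each subject underwent 4 total days of laboratory measurements".

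**Heart rate.** The Heartrate variability section says that "24 h Holter monitoring measurements have been implemented", with reference to a guideline. The same section says that HRV is compared on the half-hour rest breaks and on the night. Under Experimental group: laboratory measurements, "all measurements started between 1:30 and 2:45 pm". After Fig. 3: "Heart-rate was measured from the start of the study protocol until the CAR measurement".

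**Outcome list.** "Tertiary outcomes were changes in salivary cortisol level and heartrate variability (HRV) within the experimental group".

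**The concern.** A response is a change from a starting value. If the only morning sample comes 20 min after waking, there is nothing to subtract from it. A change in that sample between visits could reflect a change in the waking level, a change in the rise, or both, and the data cannot separate them. Any reported effect of the workstation on the awakening response would be unsupported, although the article twice gives that response as the reason for the sample.

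The recording length raises a smaller question of the same kind. A recording that begins in the early afternoon and ends shortly after waking cannot have run for 24 h.

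Both matter beyond this trial. Objectives and Discussion offer the methods as a model for later studies, and the limitations given in the Discussion mention neither point.

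**Working it through.** **1. Saliva count (reproduces Table 1).** Inputs from Measurement protocols: one sample at the end of the initial break, one after each of five blocks, one after the final break, one the next morning.

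- Laboratory: 1 + 5 + 1 = 7
- Per visit: 7 + 1 = 8
- Over 4 visits: 8 × 4 = 32

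This matches the printed 8 (32). The count closes exactly, so there is no room for an unlisted sample at waking.

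**2. What the morning sample identifies.** Let W be the cortisol value at waking and R the rise over the next 20 min. The sample is S = W + R. Between two visits, ΔS = ΔW + ΔR. Only ΔS is observed, so this is one equation in two unknowns. For example, ΔS = 0 is compatible with any ΔR that is offset by ΔW = −ΔR.

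The laboratory samples cannot stand in for W. The initial break, the five blocks with their 5 min breaks and the final break take at least 30 + 5 × (30 + 5) + 30 = 235 min, ignoring familiarisation and questionnaires. With a start at 13:30 to 14:45, the last laboratory sample falls no earlier than 17:25 to 18:40 on the day before.

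Result: a rise is computable at 0 of 4 visits, and a level 20 min after waking at 4 of 4.

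**3. ECG duration (the stated 24 h does not reproduce).** Duration = (24:00 − start) + waking time + 20 min. The start is 13:30 to 14:45. The waking time is not given, so 05:00 to 09:00 is assumed.

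| Start | Waking 05:00 | Waking 09:00 | Waking needed for 24 h |
|---|---|---|---|
| 13:30 | 15.8 h | 19.8 h | 13:10 |
| 14:45 | 14.6 h | 18.6 h | 14:25 |

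The range is 14.6 to 19.8 h, or 61% to 83% of 24 h (14.6/24 and 19.8/24). A full 24 h would need waking after 13:00, while Table 1 ends the recording on the following morning.

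The laboratory measurements section also describes the visit as early evening, which conflicts with its own 13:30 to 14:45 start. If 17:00 to 18:00 is assumed for that, the recording lasts 11.3 to 16.3 h, which is further from 24 h.

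**4. Planned HRV segments against the window.** The two half-hour rests lie within the laboratory session, and the night lies between that session and waking. Both are inside the recording under every start and waking time above.

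**The case against.** The strongest reply is that neither the awakening response nor a 24 h HRV index appears in the outcome list. A reader might infer from the two discrepancies that the tertiary outcomes cannot be obtained at all. The documents do not support that. Outcomes names salivary cortisol level, which eight samples per visit provide, and HRV, which the recorded segments provide. The morning level is also taken at the same interval after waking at every visit, so comparing it between phases is legitimate, provided it is called a level. This part of the reply stands and limits the point to the awakening response.

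A reader might likewise infer that the HRV comparison is compromised because the recording is short and misses the working morning. That does not follow. No 24 h index is planned, and the segments to be compared are covered. The true window can also be read from the Table 1 footnote and the text after Fig. 3. What remains for HRV is one inaccurate description.

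It can also be said that the source cited for the awakening response is not at hand and might define it differently. The point does not depend on that source. It needs only the ordinary meaning of a response as a change, together with the article's own sampling schedule. No claim is made here about how large the awakening response is or how it behaves.

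Finally, this is not a detail that a condensed article leaves to a fuller document: the article states the purpose, the time point and the full sample count.

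**Conclusion.** The point holds for the awakening response. The article says that the morning sample serves to detect it, and the design yields a post-waking level at all four visits and a response at none. This rests on the sampling schedule alone and needs no assumption about waking time. Both tertiary outcomes as listed remain measurable, and the primary and secondary outcomes are untouched.

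The 24 h Holter statement is a minor inconsistency. The recording lasts about 15 to 20 h if participants wake between 05:00 and 09:00, and no morning waking time gives 24 h. No planned HRV comparison changes as a result.

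**What to change.** - Analyse and report the morning sample as salivary cortisol 20 min after awakening. Remove the awakening response as its stated purpose in the Salivary cortisol level section and after Fig. 3, draw no conclusion about that response, and list the missing waking sample among the limitations.
- Replace the 24 h Holter description with the window actually recorded, and reconcile the two visit times given in the laboratory measurements section. Report HRV on the rest breaks and the night, as already planned, without calling it a 24 h measurement.

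Trial status says that measurements are complete and the study is in data analysis, so adding a sample at waking is no longer possible here. For later studies that adopt the method and want the awakening response, a sample at waking would raise the count from 8 (32) to 9 (36) per participant.

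The cost is wording only. The downside is that the awakening-response claim and the 24 h label are given up.

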### Statistical analysis

Statistical analyses will be conducted using SPSS version 21 for windows (SPSS, Chicago, IL). Standard statistical methods will be used for calculations for means and standard deviations. Pre- and post- intervention differences will be calculated for sitting time and physical parameters. Paired t-tests will be used to show differences between pre- and post- conditions when the normality condition is satisfied. If not, Mann-Whitney-U tests will be used for pre-post comparison. For cognitive parameters, ANOVA with repeated measures will be used to test whether the different conditions have any effects on the outcome parameters assessed. To reduce learning effects the first block of the test-battery will be ruled out for analysis. When appropriate, post-hoc analyses will be conducted. The effects of time, group and interaction between both variables will be evaluated. To test for normality and homogeneity of variance, Shapiro-Wilk-test and Levene-test will be used, respectively. In general, two-sided tests with an alpha risk of 0.05 and a beta risk of 0.2 are to be accepted.

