### Randomization and blinding

After the baseline assessment was completed, the participants were randomly allocated to either the intervention or the control (no intervention) arm in a 2:1 ratio (Fig. 1) by means of a covariate adaptive randomization [30]. Based on previous findings [31], ‘company’ has been determined as a stratum and thus participants were balanced across companies (i.e., 3 participants for each company). On a second level, intervention participants were assigned to either the first (intervention first) or the second (control first) intervention group. Due to the nature of the intervention, participants were not blind to their allocation.

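### The test stated for sitting time compares pre with post, while the primary outcome compares the change with the own control period and with the control group

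*Protocol article*

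**What the plan says.** The Outcomes section fixes the primary comparison: "Primary outcomes were changes in sitting time after 23 weeks in the experimental group compared with its own control period and the control group". That is two contrasts, one within person between periods and one between groups.

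The design supports both. Of 18 participants, two thirds go to the experimental arm and one third to a control arm without intervention. The experimental arm is then split by order: "On a second level, intervention participants were assigned to either the first (intervention first) or the second (control first) intervention group". The Outcome measures section calls this a cross-over with four laboratory days per subject, that is, a pre and a post measurement in each of two periods.

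The Statistical analysis section treats sitting time as follows: "Pre- and post- intervention differences will be calculated for sitting time and physical parameters". The test is then named: "Paired t-tests will be used to show differences between pre- and post- conditions when the normality condition is satisfied". The fallback for non-normal data addresses the same comparison: "Mann-Whitney-U tests will be used for pre-post comparison". Next come a repeated-measures ANOVA introduced for the cognitive parameters, the exclusion of the first test block, and post-hoc tests. Only then does the article say "The effects of time, group and interaction between both variables will be evaluated".

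**The concern.** The article does name a test for sitting time, so this is not a detail left to a fuller plan. The named test asks whether sitting time after the intervention differs from sitting time before it. The primary outcome asks whether that change differs from the change seen without the intervention.

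The two questions have the same answer only if sitting time would not move without the new desks. Here that cannot be taken for granted. Participants know their allocation, and Table 1 lists sitting time as obtained by interview questionnaire (IPAQ-long). They also know that they are being observed. The control periods and the control group are in the design to separate such shifts from the effect of the desks, and the stated test uses neither. The trial could report a significant primary result that no comparison with a control condition supports. Two analysts working from the same section could also report different primary results.

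**Working it through.** **1. The plan's own figure.** The Sample size section gives 12 subjects for a 90 min difference (two-sided 5%, power 80%, 20% loss). It states no SD and no test, so the figure cannot be reproduced. Working backwards for a paired t-test, 10 evaluable people need a standardised difference of 0.996, which implies an SD of the difference of 90/0.996 = 90 min. With 9 evaluable people the values are 1.067 and 84 min. I use 90 min below only to express drift in minutes.

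**2. What each analysis estimates.** Let τ be the effect of the desks on the change over a period, and δ a shift that would occur anyway in everyone.

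| Quantity | Expected value |
|---|---|
| Change in the intervention period | τ + δ |
| Change in the own control period | δ |
| Change in the control group | δ |
| Stated test: pre vs post, intervention | τ + δ |
| Primary contrast (a): intervention minus own control | (τ + δ) − δ = τ |
| Primary contrast (b): intervention minus control group | (τ + δ) − δ = τ |

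The stated test therefore has the null hypothesis τ + δ = 0, not τ = 0.

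**3. False-positive rate when τ = 0.**
- Number of people: the experimental arm is 2/3 × 18 = 12. With 20% loss, 12 × 0.8 = 9.6, taken as 10.
- Drift d = δ/SD of the change, set at 0.25 and 0.5. These sizes are assumptions. On an SD of 90 min they are 22.5 and 45 min.
- The paired t statistic is non-central t with n − 1 degrees of freedom and non-centrality d√n. The rejection probability is P(|T| > t critical), with critical values 2.262 (n = 10) and 2.201 (n = 12).

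| n | d | d√n | Rejection probability |
|---|---|---|---|
| 10 | 0 | 0 | 5.0% |
| 10 | 0.25 | 0.79 | 10.9% |
| 10 | 0.5 | 1.58 | 29.3% |
| 12 | 0.25 | 0.87 | 12.4% |
| 12 | 0.5 | 1.73 | 35.3% |

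**4. Sensitivity to the common-drift assumption.** The two sequences receive the intervention in different halves of the study, so a calendar effect need not be the same for all. I simulated 12 people (6 per sequence) with no effect. Drift of 0.5 SD in one half only gives 11%. Opposite drifts of 0.5 SD in the two halves give 3%. The higher rates in step 3 therefore need a shift common to both halves.

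**5. Why period belongs in contrast (a).** Let the shifts in the two periods be δ1 and δ2. Intervention minus own control has expectation τ + (δ1 − δ2) in the intervention-first sequence and τ − (δ1 − δ2) in the control-first sequence. Half the sum of the two sequence means is τ, whatever δ1 and δ2 are.

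**The case against.** The strongest defence is the sentence on time, group and interaction. It names no outcome, and the sentences after it, on normality, variance homogeneity and general error rates, clearly apply to everything. A time-by-group interaction on pre and post sitting time is the control-group contrast. This stands in part. On that reading (b) is covered, and it would be too strong to say that the section offers neither contrast under any reading. But the sentence sits at the end of the cognitive ANOVA, and even read generally it gives neither the own-control-period contrast nor a period effect. One could also suppose that the paired t-test is meant for intervention-period against control-period differences. That would give (a), but the text says pre against post, both for the test and for its fallback.

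A second objection is that the drift sizes come from nowhere in the article, and that season is a weak source of common drift because the sequences are staggered. Both are right. The rates illustrate the consequence and do not predict it. Shifts from observation or self-report could still be common to everyone.

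A reader might infer four further faults that the article does not support:
- **Company.** The article says that "participants were balanced across companies (i.e., 3 participants for each company", and company is absent from the analysis text. But company is constant within a person and drops out of contrast (a). For (b), adjustment for the stratum is commonly left to the full plan.
- **Outside-work activity.** The article says "To adjust for outside of work sedentary behavior and/or physical activities, the IPAQ-long was interview administered at the beginning of each laboratory measurement day". It does not say that post-period values would be used, so the charge of conditioning on an outcome is hypothetical.
- **Practice.** The 20 repetitions in Table 1 belong to the cognitive tests. Sitting time by questionnaire is recorded four times.
- **Power lost by ignoring period.** That loss would belong to an unadjusted period comparison, which the article does not state.

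**Conclusion.** The mismatch is real and lies within the article: the Outcomes section sets two controlled contrasts, and the test stated for sitting time estimates neither. Read generously, the time-by-group sentence supplies the control-group contrast only, so the own-control-period contrast has no stated test on either reading of that sentence. This conclusion rests on the text alone.

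The size is conditional. With 10 to 12 people and a shift common to all participants of 0.25 or 0.5 SD of the change, a nominal 5% test rejects in about 11–12% or 29–35% of trials with no effect. With no common shift the test keeps its level. The article gives no information on how large such a shift would be. The point needs correcting before analysis because the primary test does not answer the primary question.

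**What to change.** In the Statistical analysis section, replace the pre-post test for sitting time by an analysis of the change over each 23-week period:

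- **Primary contrast:** intervention-period change minus own-control-period change in the experimental group, adjusted for period. Use either the two-sequence cross-over estimator or a mixed model with period as a fixed effect and participant as a random effect.
- **Second comparison, stated as separate:** intervention against the control group, with condition coded at three levels (intervention, own-control period, control group) and the pre-period value as covariate. The three levels are needed because a single control level would merge own-control periods with control-group periods, and the two contrasts could not then be separated.
- **Scope of the interaction sentence:** say which outcomes the time, group and interaction sentence covers.

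The cost is a few degrees of freedom, which is not negligible with 18 people, and some programming. No new data are needed: the four measurement days already provide a pre and a post value in each period. The change removes shifts shared by both conditions. It does not remove reporting bias that arises only while a participant has the new desks.
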